### Sample size/power calculations

The sample size calculation was approximated with a 3×3-factorial ANOVA-approach based on the primary outcome. Previous randomised controlled trials of therapy interventions have shown effect sizes ≥ .80 in similar populations for the PRWE as a result of hand therapy, however therapy starting weeks after the accident. To prove an intervention effect with about medium effect size of Cohen's f = 0.25 with an error probability α = 0.05, a power β = 0.8, a correlation between repeated measures of .05, and a nonsphericity correction at 1, n ≈ 12 people in each study arm are required for analysis. The analysis was carried out with the G*Power software (G*Power V 3.1.6 Franz Faul, Universität Kiel, Kiel, Germany). To account for potential attrition, we will inflate the sample size by 10%, resulting in a total sample size of 39 with 13 participants allocated to each group.

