The purpose of this randomized study is to determine whether explicit motor imagery or MT during the immobilization period after distal radius fracture results in a greater recovery of central aspects of hand function. The objective of this study is to establish the effectiveness of daily training of movement imagery with the affected arm (MP) or the healthy arm (MT). It will also be examined whether enhanced functional recovery of the hand due to MP or MT is also associated with increases in the amount of activities of daily living. It will be investigated whether the benefit of motor-cognitive approaches for distal radius fracture patients is related to their individual differences in motor imagery ability.

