### Statistical analysis

Data will be analyzed using (M)ANOVA with repeated measures to ascertain the effects of therapy on outcome variables and to follow improvements individually in time. An Intention-to-treat principle will be applied. Missing data will be replaced by an imputation method for missing measurements.

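### The 80% power holds for f = 0.25 as the likely G*Power interaction routine defines it, but there f = 0.25 means an arm difference of about 1.1–1.3 SD, not a medium one

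*Protocol article*

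**What the plan says.** The section on sample size and power states: "The sample size calculation was approximated with a 3×3-factorial ANOVA-approach based on the primary outcome". The target is given as "To prove an intervention effect with about medium effect size of Cohen's f = 0.25", with "an error probability α = 0.05, a power β = 0.8" and "a correlation between repeated measures of .05, and a nonsphericity correction at 1". The result is "n ≈ 12 people in each study arm are required for analysis", raised to 13 per arm (39 in total) for attrition. Just before this, the paragraph gives its background: "Previous randomised controlled trials of therapy interventions have shown effect sizes ≥ .80 in similar populations for the PRWE".

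It does not say whether the interaction, the within-patient or the between-group test was sized, in what metric the .80 is expressed, or what f = 0.25 means as a difference between arms. The Background asks whether motor imagery or mirror therapy "results in a greater recovery of central aspects of hand function", and the Statistical analysis section plans repeated-measures ANOVA or MANOVA.

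**The concern.** The label medium for f = 0.25 comes from between-group comparisons, where it is about 0.5 SD between two groups (d = 2f). Set beside earlier effects of .80 or more, f = 0.25 reads as the cautious choice. If the calculation was for a group-by-time interaction, f measures something else: centring over groups and again over visits shrinks a real arm difference, so a given f stands for a much larger one.

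The trial's question is about arm differences. A reader who takes the paragraph at face value would expect an 80% chance of detecting a medium difference in recovery between an active arm and control, and would weigh a null result accordingly.

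**Working it through.** **Inputs.** From the sample-size section: k = 3 groups, m = 3 occasions, f = 0.25, alpha 0.05, power 0.80, sphericity (correction 1), correlation ρ printed as .05, 36 patients for analysis. Assumed: ρ = .5 (the value that reproduces 36) and ρ = .7 as a sensitivity case.

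**Step 1. Which routine gives 36?** For the interaction, λ = N·m·f²/(1−ρ), df1 = (k−1)(m−1) = 4, df2 = (N−k)(m−1).

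- ρ = .05, N = 36: λ = 36 × 3 × 0.0625 / 0.95 = 7.11, df 4 and 66, power 51%. Reaching 80% takes 63 patients. The within-patient test needs 51 and the between-group test 60.
- ρ = .5, N = 36: λ = 6.75 / 0.5 = 13.5, power 82.3%. The smallest N is 35, which rounds to 36 = 12 per arm. At this ρ the within-patient test needs 28 and the between-group test 106.
- G*Power's alternative effect-size options (Cohen, SPSS) for the interaction need 98 and 101.

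So the plan's figure is reproduced by the 3×3 interaction with ρ = .5, and not with the printed .05.

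**Step 2. What f = 0.25 means there.** f is the root mean square of the doubly centred 3×3 cell means, divided by the SD at one visit. Let control stay at 0 (relative to the common time course) and let D be the active-minus-control difference in change, in SDs.

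- Sustained gain, both active arms (0, D, D): f = √(2/9) × √(2/9) × D = 0.222 D, so D = 0.25/0.222 = 1.125.
- Linear gain, both arms (0, D/2, D): f = √(2/9) × √(1/6) × D = 0.192 D, so D = 1.30.
- Staggered, one arm (0, D, D) and the other (0, 0, D): six of the nine residuals are ±D/3, so f = √(6/9 × 1/9) × D = 0.272 D, and D = 0.92.

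The first two results are the same if only one active arm works. None of the conversions involves ρ.

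**Step 3. Power at N = 36**, putting f = c·D into the formula of Step 1. Example: sustained, D = 0.5, ρ = .5 gives f = 0.111, λ = 36 × 3 × 0.01235 / 0.5 = 2.67, power 20.6%.

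| D | ρ | Sustained | Linear | Staggered |
|---|---|---|---|---|
| 0.5 | .05 | 12.5% | 10.4% | 16.9% |
| 0.5 | .5 | 20.6% | 16.2% | 29.9% |
| 0.5 | .7 | 33.1% | 25.2% | 48.5% |
| 0.8 | .05 | 27.0% | 20.8% | 39.8% |
| 0.8 | .5 | 49.6% | 37.9% | 69.2% |
| 0.8 | .7 | 74.4% | 60.1% | 91.0% |

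Simulation of the sustained and linear patterns (20,000 runs, 12 per arm, ρ = .5) agrees: 20% and 16% at 0.5 SD, 49% and 39% at 0.8 SD, and 82% at 1.125 SD (sustained) and 1.30 SD (linear).

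**Step 4. Other readings of medium.** In a three-group between-group comparison with both active arms equal, f = 0.25 means D = 0.25/√(2/9) = 0.53. Interaction power for that is 23% (sustained) or 18% (linear) at ρ = .5. A one-way ANOVA with f = 0.25 on change scores has 23% power at 36 patients. A two-sample t-test on change at 0.5 SD has 22% (12 against 12) or 28% (24 against 12). All fall far below 80%.

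**The case against.** **No arithmetic error.** The plan states power for f = 0.25, medium is the usual label for that f, and the likely routine does give 82%. A reader might infer that the 80% is miscalculated. With ρ = .5 it is not. What stands is that the paragraph attaches the label to an intervention effect without saying what arm difference it stands for.

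**Routine and correlation are inferred.** The printed .05 leads to no version of 12 per arm, and other correlations open other routes: at ρ = .35 the within-patient test also gives 36, although it does not compare arms. The interaction with .5 is the most plausible reconstruction, not a documented fact. The SD conversion does not depend on ρ but does depend on the interaction having been the test.

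**The .80 is not comparable as printed.** A reader might infer that the plan sized the trial for an effect larger than the one it cites, or that the trial has at best an even chance of detecting that effect. The documents support neither. The metric of .80 is not stated and could be a pre-post effect. Even read as a between-arm difference in change, power ranges from 21% to 91% in the table above. With all four scheduled visits, gain from the third visit on and ρ = .7, it is 87%. If each arm gained at one different visit only, f = 0.25 would need just 0.71 SD.

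**Consequences.** The Conclusions section already foresees inconclusive results and a second trial. Nothing says that a null result will be read as excluding a medium effect, or that a later trial will be sized from this paragraph.

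**Conclusion.** The point holds as one about what the power statement means. If the 12 per arm come from the 3×3 interaction, f = 0.25 corresponds to about 1.1 SD (sustained gain) to 1.3 SD (linear gain) between an active arm and control, and 0.92 SD under the staggered pattern. For a conventionally medium difference of 0.5 SD, power at 36 patients and correlation .5 is about 16–21%, or 30% if staggered. Under the simple patterns it is about 10–13% at correlation .05 and 25–33% at .7. No case in the table comes near 80% at 0.5 SD.

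The statement about .80 is conditional. Only if it is a between-arm standardised difference in change is power for it about 38–50% under the simple patterns at correlation .5, 69% if staggered, 21–27% at .05 and 60–74% at .7 (simple patterns).

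Assumptions: sphericity, equal SDs, three occasions, 36 analysed, and medium taken as 0.5 SD.

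**What to change.** Keep 39 patients and reword the sample-size paragraph:

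1. Settle the correlation that was actually entered. This must be part of the same edit: at .05, 36 patients give 51% power for f = 0.25, and any detectable difference quoted for 80% power would contradict the printed value.
2. Name the group-by-time interaction as the test sized, if that is confirmed.
3. Replace the medium label with the arm difference implied under a stated pattern and correlation. For example: with correlation .5, 36 analysed patients give about 80% power for a difference in PRWE change between an active arm and control of about 1.1 SD (sustained gain) to 1.3 SD (linear gain), and 16–21% for 0.5 SD.
4. State the metric of the cited .80, or do not set it beside f.
5. Add that a non-significant result does not exclude a medium arm difference.

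The cost is a few sentences, with no extra patients or measurements. The downside is a less favourable statement of the detectable effect.

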### Procedure

All patients give written informed consent prior to the study. Before randomization, the patients complete the Controllability of Motor Imagery Test[47] to control for the ability to perform and control a mental image of a movement, which is essential for successful imagery training. After baseline assessment, randomization is performed by an independent department (Department of Biometrics at Ulm University).Assessment of primary and secondary outcomes takes place upon entry to the study (T1) by a blinded assessor and is repeated after 3 weeks (T2), 6 weeks (T3), and 12 weeks (T4, follow-up) after the beginning of the training program (see Figure 1).

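### The printed sample-size inputs do not give 12 per arm: at a repeated-measures correlation of .05 they imply about 51% power at 36 patients, while a correlation of .5 reproduces 36

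*Protocol article*

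**What the plan says.** All inputs are in the Protocol article, under Sample size/power calculations.

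- Design: "The sample size calculation was approximated with a 3×3-factorial ANOVA-approach based on the primary outcome".
- Effect size: "about medium effect size of Cohen's f = 0.25".
- Type I error: "with an error probability α = 0.05".
- Power: "a power β = 0.8", read here as power 0.80.
- Correlation, nonsphericity correction and result: "a correlation between repeated measures of .05, and a nonsphericity correction at 1, n ≈ 12 people in each study arm", which is 36 patients in total.
- Allowance for dropout: "we will inflate the sample size by 10%, resulting in a total sample size of 39", or 13 per group.

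The software is named as G*Power 3.1.6. The article gives no other value for the correlation. It does not say whether the effect powered is the group-by-time interaction, the group effect or the time effect.

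**The concern.** Every input is printed, so the calculation can be repeated. In a repeated-measures design, the correlation strongly affects the power for a difference in change between groups. A value of .05 means that a patient's successive scores are almost unrelated, which gives little gain from measuring the same patient repeatedly. With a correlation that low, 12 per arm looked too few for f = 0.25.

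This paragraph is the only justification in the article for enrolling 39 patients. Either the correlation is printed wrongly by a factor of ten, or the sample size falls short of its stated power. A reader cannot tell which, and so cannot tell what power the trial was planned to have.

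**Working it through.** **Inputs, all from the sample size section:** groups k = 3, measurements m = 3, f = 0.25 (f² = 0.0625), alpha = 0.05, target power 0.80, correlation ρ = .05, nonsphericity correction ε = 1, stated N = 36.

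**Formulas (noncentral F, as in G*Power's repeated-measures ANOVA)**

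- Group-by-time interaction: λ = f²·N·m·ε/(1 − ρ), df1 = (k − 1)(m − 1)ε, df2 = (N − k)(m − 1)ε.
- Within-subject (time) effect: same λ and df2, df1 = (m − 1)ε.
- Between-groups effect: λ = f²·N·m/(1 + (m − 1)ρ), df1 = k − 1, df2 = N − k.

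**Step 1: try to reproduce the plan's figure with the printed inputs (interaction).**

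- f²·N·m = 0.0625 × 36 × 3 = 6.75.
- λ = 6.75/0.95 = 7.105, df 4 and 66, power 0.514.
- At N = 39, power is 0.554.
- The smallest balanced N for 80% is 63 (21 per arm, power 0.801); N = 60 gives 0.777.

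The stated 36 is not reproduced. A simulation of 20,000 trials at N = 36 gave 0.512.

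**Step 2: try other readings at ρ = .05, with three groups and f = 0.25.**

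| Measurements | Effect | Power at N = 36 | N for 80% |
|---|---|---|---|
| 3 | interaction | 0.514 | 63 |
| 3 | between groups (λ = 6.75/1.10 = 6.136) | 0.553 | 60 |
| 3 | within subject | 0.641 | 51 |
| 4 | interaction | 0.584 | 54 |
| 4 | between groups | 0.665 | 48 |
| 4 | within subject | 0.717 | 45 |

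With two measurements, every effect needs 63 or more. The software's other conventions for entering the effect size need 60 to 222. Raising alpha to 0.10 for the three-measurement interaction still needs 54. No reading at .05 gives 36.

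**Step 3: change only the correlation (interaction, m = 3).**

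| ρ | Power at N = 36 | Smallest balanced N for 80% |
|---|---|---|
| .05 | 0.51 | 63 |
| .3 | 0.66 | 48 |
| .45 | 0.78 | 39 |
| .5 | 0.82 | 36 |
| .55 | 0.87 | 33 |

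At ρ = .5, λ = 6.75/0.5 = 13.5 and power is 0.823. N = 33 gives 0.781, so 36 is exactly the smallest balanced total. The simulation gave 0.821. Power at N = 36 reaches 80% once ρ is about 0.47.

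The match at .5 holds only for the interaction. At ρ = .5, the between-groups effect with three measurements has λ = 6.75/2 = 3.375 and power 0.329 at N = 36, and needs 108. The effect tested therefore has to be named.

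**The case against.** The strongest reply is that .05 is a slip for .5. With every other input as printed, .5 gives exactly 12 per arm, and such a match is unlikely to be chance. On that reading the sample size stands and the repair is one digit. Most of this is right, and it limits what can be claimed. It does not remove the point: the misprint is an inference, the article prints only .05, and the paragraph is wrong as it stands under either explanation.

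A reader might infer more from the mismatch. The documents do not support these stronger readings:

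- **The trial really has 51% power.** Actual power depends on the true correlation of the wrist scores, which the article does not report. The 51% follows only from the printed input.
- **Using three measurements is a further defect.** After baseline, assessment "is repeated after 3 weeks (T2), 6 weeks (T3), and 12 weeks (T4, follow-up", which makes four visits. But the calculation is described as an approximation, and under the same model a fourth visit raises interaction power at N = 36 (0.514 to 0.584 at .05; 0.823 to 0.890 at .5). Using three is the cautious choice.
- **The dropout allowance fails.** 12 × 1.1 = 13.2, rounded to 13. The totals 36 × 1.1 = 39.6 and 36/0.9 = 40 differ from 39 by at most one patient. With 39 × 0.9 = 35.1, about 35 patients remain, and at ρ = .5 they still give 0.809.
- **The nonsphericity correction of 1 is an error.** It is stated openly, and nothing in the article contradicts it. Preferring a lower value is a matter of judgement.
- **A null result would be read as proof of no effect.** The article plans no such inference. Its Conclusions section allows for inconclusive results and a second trial.

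**Conclusion.** The point holds as an internal inconsistency in the power statement for the primary outcome. The printed inputs imply about 51% power at 36 patients and 55% at 39 for the interaction, against the stated 80%. They require 63 patients, 27 more than the 36 stated. The between-groups and within-subject effects do not rescue the figure.

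This rests on the noncentral F formulas above, f = 0.25, three groups, three measurements and no nonsphericity adjustment. A misprint of .05 for .5 is the most likely cause, because changing that one input restores 36 exactly. If so, 12 per arm is correct for the interaction, but it has little margin: power at 36 is 0.82 at .5, drops below 80% under about 0.47, and is 0.66 at .3. The documents do not establish that the sample size itself is too small.

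**What to change.** Correct the sample size paragraph.

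1. State the correlation that was entered in the software, and name the effect tested (group-by-time interaction, if that is what was used).
2. If the value was .5, replace .05, give the basis for .5, and add that power at 36 patients falls below 80% for correlations under about 0.47 (0.66 at .3).
3. If .05 is meant, keep it and restate the power as about 51% at 36 patients and 55% at 39.

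No extra enrolment and no change to the design or analysis is asked for. The only cost is a corrected paragraph, with a power statement that may be less favourable.

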### Statistical analysis

Data will be analyzed using (M)ANOVA with repeated measures to ascertain the effects of therapy on outcome variables and to follow improvements individually in time. An Intention-to-treat principle will be applied. Missing data will be replaced by an imputation method for missing measurements.

## Discussion

This trial is due to deliver results by the end of 2014. Up to now, participants have shown a very high compliance, less than 10% resigned (1 in MP group, 1 in CG). Recruitment is more difficult than expected, partly caused by a very short hospital stay combined with the dependency of prompt communication of new adequate patients, partly due to an exceptionally mild winter (less falls), and partly due to communication deficits. Therefore, the intervention period turns out to be several months longer than initially planned.

## Conclusions

Study outcomes should be carefully analyzed, possibly leading to further adjustments of the intervention protocol or to a second trial that is ruling out the assumed reasons for inconclusive results like a high rate of intercurrent diseases. A positive study outcome should be tested in a large multi-center trial.

## Authors’ original submitted files for images

Below are the links to the authors’ original submitted files for images. Authors’ original file for figure 1 Authors’ original file for figure 2
